### **13.8.1 Rules for Handling any SAE:**

- The first reader will evaluate the skin test sites, measure induration and complete the Skin Test Reading Form. The second reader will then perform the same evaluation and measurements, and record the data. The MO, nurse or paramedic will then examine and interview the subject and complete the Follow-up Reaction Reading Form. Any of these staff members that become aware of an SAE will notify the attending physician.
- In the case that an SAE occurs, no further skin tests will be administered until the IRB has been informed.
- The attending physician will immediately examine the subject.
- The staff member and attending physician will complete the AE Form and the SAE Form; the principal investigator will be required to sign the SAE Form.

- The staff member is responsible for immediately reporting the SAE to the SC.
- The SC is responsible for verifying information and ensuring that all necessary information is obtained to clarify the event and determine its relevance to the study.
- The SC will notify the ISM no later than 24 hours after receiving the report of the SAE. The ISM will review the SAE upon notification of its occurrence.
- The SC or Principal Investigator will complete an SAE report and e-mail it to the DMID PO, DMID ORA, SMC, and the data center. In the event of a death, an autopsy report and terminal medical report should also be supplied. Updated reports generated by the SC must also be sent.
- The ISM will discuss any SAE that is possibly, probably, or definitely related to the study, and any death, whether related or not, with the DMID PO within 3 working days.
- The DMID PO will convene the SMC if necessary for further review.
- The Sponsor will then notify the investigator at CSU, the ORA, and the FDA.
- The SC will notify the NHRC, while the CSU investigator will notify the CSU IRB.
- Prior to reconvening the study, the SC must receive approval from the DMID PO.

### **13.8.2 Rules for Handling Multiple AEs:**

Steps for handling AEs are similar to those outlined above for SAEs, but do not require the same level of urgency in reporting. AEs are identified by attending staff members and treated according to specifications outlined in the MOO. The attending physician is not notified unless the event becomes severe. The staff member completes the AE Form and informs the SC, who then informs the ISM. The ISM is responsible for reviewing all AEs and reporting concerns to the SC or Principal Investigator. If a pattern of AEs is indicative of a safety concern, the ISM can temporarily suspend enrollment of further subjects, pending discussion with the DMID PO and the SMC. This situation could pertain to the entire study, a specific study group, or individual study subjects, depending on the response to certain antigens and/or antigen dosages.

### **13.8.3 Safety Outcomes**

The following safety outcome measures will be monitored: Measurement of induration, indication of erythema, measurement of local reactions, measurement of systematic reactions, and monitoring for AEs and SAEs. Each measure of safety is controlled by specifications for an AE and SAE. Monitoring safety outcome measures is performed during each study visit, up to day 3 for Stage A, and up to day 7 for Stages B and C. Reactions to the antigens that are assessed as being severe will be followed-up to day 28, or until resolved or stabilized. If a subject responds to any skin test antigen greater than 10mm in

diameter at any study visit, they will be followed-up to day 28, or until resolved or stabilized.

#### **13.8.4 Statistical Rules to Halt Enrollment**

N/A

### **13.9 Analysis Plan**

Data for this study will consist of inclusion/exclusion documentation, medical histories used to determine leprosy and TB status, basic demographic information (age, race and gender), reactions to the antigens used to assess safety (erythema, itching, pain/tenderness, bleeding, urticaria, infection and blistering), induration as a measure of response for detecting leprosy, and adverse events. An important immunological addition will be the IFN- $\gamma$  responses to at least the skin test antigens and Tuberculin/PPD, and the antibody response to the leprosy specific PGL-I antigen in participants in Stage C.

Study participants are randomized to different templates for antigen administration in order to add blinding to evaluation of outcomes and reduce observer bias. Analyses will be conducted to determine if there are important differences based on randomization within any study group. This factor will only be included in any of the subsequent analyses discussed below if there are clear suggestions of possible differences attributable to the randomization process.

Whenever appropriate, analyses will be conducted within study group and by combining groups that are similarly expected to have the same type, positive or negative, response to the test antigens.

#### **13.9.1 Study Enrollment and Compliance**

Descriptive analyses will be used to summarize the characteristics of the study cohorts and their completion of all study procedures. This will include basic demographic data and critical elements of the medical histories taken at the time of study enrollment, prior to antigen testing. Study participants are randomized to different templates for antigen administration in order to add blinding to evaluation of outcomes and reduce bias.

Sample size computations have assumed a 10% loss to follow-up, a generous estimate. Losses will be investigated to try and determine if there is a systematic bias of any type, but no imputation methods to adjust for losses are currently planned.

#### **13.9.2 Safety**

Safety analyses will summarize the proportion of study participants with erythema, itching, pain/tenderness, bleeding, urticaria, infection and blistering for each time point and antigen combination. (Reaction rates were very low in Stages A and B involving healthy controls, but may be higher in Stage C of this study.) If reaction rates are high, they will be compared across groups using categorical methods to test for statistically significant differences by group.

Longitudinal methods, such as a Generalized Estimating Equations (GEE) version of logistic regression will be considered as well.

Adverse Events will be coded by the Medical Dictionary for Regulatory Activities (MedDRA®) for preferred term and system organ class, and classified by their possible association with antigen testing. AEs will be tabulated by possible relationship to antigen and greatest reported intensity. They will be listed by subject identification code, antigen injection date, event description, MedDRA® preferred term, onset date and time, end date, maximal intensity, antigen association, action taken, outcome, resolution and brief notes. AEs will be tabulated by MedDRA® preferred term to determine if it is appropriate to conduct further analyses based on this classification.

### 13.9.3 Diagnostic Sensitivity/Specificity

These analyses will involve the selection of a cut-off for diagnostic testing, using the test antigens by dose, construction and comparison of ROC curves, and the determination of the sensitivity and specificity of the test antigens based on the selected cutoff points. This work will be based on the induration stimulated by the test antigens.

The text *Statistical Methods in Diagnostic Medicine* (37), will serve as a reference for most of the methods used in these analyses. An important assumption for many of these methods is that the distribution of the outcome measure (induration) follows an approximate binormal distribution, i.e. a combination of two normal distributions, one for the population with the condition of interest and another for the population without the condition. This assumption will be examined and exploited if it is met. Assuming that there is not a complete or virtually complete separation between the groups in their response, methods described by Schaefer, et.al. (38) will be examined to construct a cut-off for each of the antigens at each dose. For each cutoff the 95% confidence interval for the sensitivity and specificity based on this cutoff will be constructed. ROC curves will be constructed, the area under the curve and its 95% confidence interval computed and the antigens/doses will be compared to determine if there is a statistically significant difference in area.

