Stages A and B will serve to re-confirm the U.S. data on the safety of these products, which will be done in two steps - first in 10 subjects (Stage A) and then in 90 subjects (Stage B). Having found an optimal safe dose for each antigen, both reagents will then be tested in 80 leprosy patients, 40 contacts of leprosy patients, and 40 tuberculosis patients (Stage C), and the results compared with the licensed TB reagent tuberculin/PPD. If the study results indicate that one or both leprosy skin test antigens show specificity and sensitivity in the order of 90% or above, future studies will be planned to measure the extent of leprosy infection in communities around the world, particularly the high prevalence countries of India, Nepal, Brazil, and some of the African countries.

Study Hypothesis: Both leprosy skin test antigens, MLSA-LAM and MLCwA at doses of 1.0µg and/or 0.1µg, will be safe and efficacious as diagnostic-epidemiological tools to detect and treat patients earlier and to measure the extent of leprosy infection in human subjects living in a leprosy endemic area.

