## 4 STUDY DESIGN

This study will be a double-blind Phase II clinical trial conducted in three Stages (A, B, and C). Antigens are coded, and subjects are randomly assigned a template for placement of skin test antigens. Stage A will provide an initial indication of the safety of the two new test antigens in ten healthy members of this leprosy endemic population (five subjects per antigen at two dosages each). Stage B will expand this analysis by an additional 90 healthy subjects (45 subjects per antigen). If any of the subjects in Stage A or B show ulcerations at the 1.0 $\mu$ g dose of MLSA-LAM or MLCwA test sites, then only the 0.1 $\mu$ g dose will be used for Stage C. The final stage, Stage C, is divided into two parts. The first part, Stage C-1, will assess the safety of both antigens at the high dose (1.0 $\mu$ g) in populations at a higher risk of developing ulcerations at the skin test site. A total of eighty subjects will be recruited: 20 household contacts of BL/LL leprosy patients, 20 BL/LL leprosy patients, 20 BT/TT leprosy patients, and 20 TB patients. The second part, Stage C-1b, is a continuation of Stage C-1 with the same number of subjects recruited from the same groups to assess the reactivity of both antigens at the low dose (0.1  $\mu$ g). Safety data will be collected following each stage and reviewed by the SMC. A report will be forwarded to DMID, NHRC, and CSU IRB for review and approval.

This study will define a positive skin test reaction for MLSA-LAM and MLCwA and this definition will be used in estimating sensitivity and specificity for each skin test antigen and dosage. The skin test reactions (as compared to reactions from tuberculin/PPD, and Phase I studies of MLSA-LAM and MLCwA) will vary among the groups participating in this study. It is expected that the BT/TT leprosy patients and healthy contacts of leprosy patients will have larger indurations at both *M. leprae*-derived antigen sites, and a variable reaction at the site of the tuberculin/PPD. The non-contacts, BL/LL leprosy patients, and tuberculosis patients will have smaller indurations at all leprosy skin test sites, and a variable reaction at the site of tuberculin/PPD. Finally, the tuberculosis patients will react with a large induration at the tuberculin/PPD site.

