##### Stage B

- Primary objective:  
To evaluate the safety of the two leprosy skin test antigens in larger numbers of healthy individuals without known exposure to clinical leprosy or tuberculosis, living in a region endemic for leprosy.
- Secondary objectives:
  - To compare responses to the leprosy skin test antigens to those of PPD/tuberculin, in order to determine if there is differentiation between the two in this population with presumed exposure to indigenous *Mycobacterium tuberculosis*, other indigenous mycobacteria, and in some cases, subjected to BCG vaccination.
  - To combine data on skin test responses to the leprosy skin test antigens and to PPD/tuberculin, with data from an equivalent group in Stage C, to arrive at a valid definition of a positive response, versus a negative response (i.e. “cut-off” point).

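### Section 13.9.3 chooses the positivity cut-off and estimates sensitivity and specificity at it in the same small groups, with no correction for the selection

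*Protocol*

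**What the plan says.** Estimating sensitivity and specificity is a primary objective (Protocol, 3.1). Section 4 says that the study will itself define a positive reaction and that "this definition will be used in estimating sensitivity and specificity for each skin test antigen and dosage". Section 13.5 would take that definition from the observed shape of the induration distribution.

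Section 13.9.3 sets the order of work: choose a cut-off, then carry out "the determination of the sensitivity and specificity of the test antigens based on the selected cutoff points", and then: "For each cutoff the 95% confidence interval for the sensitivity and specificity based on this cutoff will be constructed". The selection rule is not fixed. A cited method "will be examined to construct a cut-off for each of the antigens at each dose", and the assumption that induration "follows an approximate binormal distribution, i.e. a combination of two normal distributions" is to be checked and used if it holds. The section names no interval method, hold-out sample, cross-validation or bootstrap.

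Section 13.6.2 rules out combining Stage C-1 with C-1b for ROC, sensitivity or specificity work, because the two stages use different doses. Section 2.2 says that if one or both antigens "show specificity and sensitivity in the order of 90% or above, future studies will be planned".

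A Stage B secondary objective (13.1.2) would combine Stage B responses "with data from an equivalent group in Stage C, to arrive at a valid definition of a positive response".

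**The concern.** A cut-off picked because it separates the observed groups well also fits their chance fluctuations. Sensitivity and specificity computed at that cut-off in the same subjects are then too high on average. The bias grows as the groups shrink, and here they are small. An interval computed as though the cut-off had been given in advance carries none of the selection uncertainty.

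What is at stake is a primary estimate and the informal 90% level that would lead to further studies. A test whose true accuracy is somewhat below 90% would reach that level more often than it should, and four antigen-dose combinations each have a chance to do so. The area under the ROC curve needs no cut-off and is not affected.

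**Working it through.** **Inputs from the protocol**
- 20 enrolled and 18 evaluable per patient group and dose, after 10% loss (13.6.1).
- Doses analysed separately (13.6.2). This gives 18 per group and dose, or 2 × 18 = 36 when two groups on the same side are combined.
- 50 non-contacts per antigen (5.1.4), or 45 after 10% loss. Added to 18 TB patients, they give 45 + 18 = 63 possible negatives per antigen and dose.

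**The plan's own precision figures**
The table in 13.6.2 gives 95% half-widths. The formula 1.96 × √(p(1−p)/n) gives, at p = 0.5, 0.75, 0.9 and 0.95:
- n = 36: 0.163, 0.141, 0.098, 0.071 (stated 0.16, 0.14, 0.10, 0.07)
- n = 72: 0.115, 0.100, 0.069, 0.050 (stated 0.12, 0.10, 0.07, 0.05)

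All eight entries match a Wald interval at a cut-off fixed in advance. The planned precision therefore contains nothing for selecting the cut-off. (The same section's bar on pooling means that one group has 18 per dose, not 36. The half-widths at n = 18 are 0.231, 0.200, 0.139 and 0.101. That is a related but separate matter.)

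**Simulation of the bias**
Assumptions, which are not in the protocol: negatives N(0, 1), positives N(d, 1), with d = 2Φ⁻¹(t), so that the best cut-off has true sensitivity and specificity both equal to t. There were 2,000 to 6,000 simulated trials per setting. Bias is the mean of observed minus true value at the cut-off chosen.

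Bias in percentage points (sensitivity / specificity) when the cut-off maximises observed sensitivity plus specificity:

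| Positives v negatives | t = 0.65 | t = 0.80 | t = 0.85 | t = 0.90 |
|---|---|---|---|---|
| 18 v 18 | 7.8 / 8.1 | 6.3 / 5.9 | 5.4 / 5.5 | 4.5 / 4.5 |
| 36 v 36 | 5.6 / 5.6 | 4.1 / 4.1 | 3.7 / 3.6 | 3.1 / 2.9 |
| 18 v 63 | 10.1 / 3.1 | 7.9 / 2.2 | 6.8 / 1.9 | 5.8 / 1.7 |

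Other rules give different results:
- Midpoint of the two group means (model-based): under 1 point in every setting.
- Observed specificity of at least 90%: specificity about 5 points too high at n = 18 and 2.5 at n = 36; sensitivity about 0.

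**Effect on the 90% level, 18 v 18**
Reaching 90% takes at least 17 of 18. With a fixed cut-off and t = 0.85, P(Bin(18, 0.85) ≥ 17) = 0.224, and for both measures 0.224² = 0.050. With the data-chosen cut-off, the simulated chance that both reach 90% is 0.12.

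**Effect on the intervals, 18 v 18, t from 0.70 to 0.90**
- Wald, data-chosen cut-off: coverage about 61 to 80%.
- Wald, fixed cut-off: about 84 to 94%.
- Exact (Clopper-Pearson), data-chosen cut-off: about 96 to 99%.

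**The case against.** The strongest reply is that the protocol names no rule that maximises observed accuracy. If the binormal model holds and is used, the bias may be negligible. The cited cut-off method may itself allow for selection; its content is not in the protocol. Resampling detail is often left to a statistical analysis plan, which is not at hand. Section 13.5 disclaims formal hypotheses, and Section 2.2 foresees a possible Phase III study to substantiate the results.

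This limits the size of the problem but does not remove it. Section 13.9.3 fixes the sequence of choosing and scoring on the same subjects, and it leaves the rule with the largest bias available after the data are seen.

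A reader might infer more than the documents support:
- **A loss of 6 to 8 points on each measure at the 90% level.** That needs an accuracy-maximising rule, 18 v 18, and true values of about 0.65 to 0.80. At 90% the same setting gives about 4.5 points. With unequal groups the bias falls mainly on the measure with fewer subjects.
- **Intervals that are too narrow whatever the method.** Wald intervals under-cover, exact intervals roughly hold, and the method is not stated.
- **An independent validation group lost from Stage C.** The Stage B objective would have pooled that group to set the cut-off; it was never a validation sample.
- **A formal 90% success criterion.** Section 2.2 offers it only as an informal prompt for later studies.

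**Conclusion.** The concern holds in a bounded form. Cut-off and accuracy come from the same subjects, about 18 per group and dose, with no stated correction. If the cut-off is chosen to maximise observed accuracy, a primary estimate is biased upward: about 4 to 6 points for each measure at 18 v 18 and true values of 80 to 90%, about 3 to 4 points at 36 v 36, and about 6 to 10 points for sensitivity with 2 to 3 for specificity at 18 v 63 over true values of 65 to 90%. Under a model-based midpoint rule the bias is under 1 point. At 18 v 18 and true values of 85%, the chance that both measures appear as 90% or more rises from 5% to about 12% for each antigen and dose.

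These sizes rest on the equal-variance binormal model and on the rule assumed. The direction follows whenever the cut-off is chosen to maximise observed performance.

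Separately, the Stage B objective refers to an equivalent group in Stage C, but Stage C enrols contacts, leprosy patients and TB patients and no healthy non-contacts.

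**What to change.** In 13.9.3:
1. State one cut-off selection rule, and the groups it uses, before Stage C codes are broken.
2. Report bootstrap or cross-validated optimism-corrected sensitivity and specificity. Repeat the cut-off search inside each resample, so that the intervals include the selection, and name the interval method.
3. Label uncorrected values as apparent.

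As an option, also report accuracy at a cut-off fixed beforehand from the Stage A and B non-contacts, who received each antigen at both doses and whose data are unblinded after Stage B (4.7). Subjects used to set that cut-off should not also be used to score its specificity. The text should also deal with the different reading windows: 69-75 h in Stages A and B against 2-4 days in Stage C.

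In 13.1.2, correct the Stage B objective that refers to an equivalent Stage C group.

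The cost is a change of wording, a little programming and slightly less favourable reported accuracy. No change to enrolment or visits is needed.

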### 13.9.4 Assay for Immune Responses

The IFN- $\gamma$  responses and leprosy specific PGL-I antigen antibody responses will be assessed as possible diagnostic tools in a similar manner to the induration outcome. The antibody response, however, will be reported on a binary scale (positive/negative) so that there will be no opportunity to construct ROC curves or statistically determine a cut-off. Additional analyses will explore the correlation between the various outcome variables and test their association with baseline covariates such as demographic variables and medical history.

## 14 ACCESS TO SOURCE DATA/DOCUMENTS

The source documents for Stage A consisted of CRFs printed on two-ply No Carbon Required (NCR) paper. For Stages B and C, the source documents consist of data collection forms derived from the electronic case report forms (eCRF). Most data on the CRFs will be obtained directly from the participant; however, to obtain the necessary information for the purposes of the diagnosis of leprosy and tuberculosis, the necessary information will be obtained from the subject's medical record. These medical records will only be accessed following permission from the person concerned, and only the specified information will be obtained.

The SC will ensure the accuracy, completeness, legibility, and timeliness of the data reported on the source documents. For Stage A, the original (white copy) of the NCR source document was forwarded to the DCC for data entry; the second (yellow) copy of the NCR source document was maintained on-site at AH. For Stages B and C, the data from the source documents are entered into the eCRFs on a laptop computer at AH and sent to the DCC on a compact disk approximately monthly. The screening form will not be entered into the database, but will be retained in locked files on-site, in the event that data on these forms need to be analyzed in the future.

As a quality control measure, the data will be checked for anomalies and inconsistencies through the DCC's Data Integrity Evaluation System. The Data Manager will send a Data Resolution Form outlining missing values, out-of-range values, and other data anomalies to the central clinical site for reconciliation of data discrepancies. Photocopies of modified forms will be sent back to the DCC for entry into the database, while a photocopy will be maintained in the subject's CRF folder.

Essential trial documents will be maintained for this trial, in compliance with ICH E6 GCP, Section 8, and regulatory and institutional requirements for the protection of confidentiality of subjects. Files will be established by the sponsor, and by each investigator to organize and retain essential documents. To satisfy FDA IND requirements, essential documents will be maintained by DMID, AH, and Colorado State University for a period of 2 years after the end of the trial.

The DMID Office of Regulatory Affairs will inform the investigators as to when these documents no longer need to be retained. Each participating site will permit authorized representatives of DMID sponsors, FDA regulatory authorities, and either NHRC or CSU IRBs to examine study records for the purposes of quality assurance reviews, audits, and evaluation of the study safety and progress.

